#### Statistical Analysis

The primary statistical analyses will directly address Aim 1 (to determine if RM is an effective treatment for chronic low back pain) and Aim 2 (to determine if FSM is more effective than RM). A separate analysis will address the third aim, to explore the ability of psychosocial, and clinical baseline characteristics of patients to predict which of them will benefit most from each type of massage and which components of each treatment are associated with superior outcomes. These analyses are described below.

We will use an intent-to-treat approach for all analyses, i.e., individuals will be analyzed by the group to which they were randomized, regardless of participation in any treatment sessions. This minimizes biases that often occur when participants not receiving assigned treatments are excluded from analyses. We will use a standard linear regression mean model (ANCOVA) of the form:

where *Y*(*t*) is the response at follow-up time *t*, *Baseline *is the pre-randomization value of the outcome measure, *Trt *includes dummy variables for the full relaxation massage and focused structural massage groups, *Time *is a series of dummy variables indicating the follow-up times, and *z *is a vector of covariates representing other variables being adjusted for. (Note that α_1_, α_2_, α_3_, and α_4 _are vectors.) The referent group in this model is the usual care group at the first follow-up time. The models will be fitted using Generalized Estimating Equations (GEE) to take into account possible correlation within individuals over time [24]. GEE protects against misspecification of the correlation within a participant's scores over time. Such analyses can incorporate data for every time point at which a patient completes a follow-up interview. However, it is important to first assess whether there is differential dropout by either assigned treatment or symptom or function level. If differential dropout occurs, we will use the method of Little to rectify possible biases that could occur [25].

Both primary outcomes (function and symptoms) will be tested at the 0.05-level, because they address separate scientific questions. Analyses of both outcomes will be reported, imposing a more stringent requirement than simply reporting a sole significant outcome. Arguments against adjusting for multiple comparisons in this situation have been made by Rothman) and others [26-28].

If we find a significant overall difference, we will localize the difference among the three groups using pairwise comparisons in accordance with our specific aims. For Aim 1, we will compare the RM group with the UC group. For Aim 2, we will compare the RM group with the FSM group. We will also compare the FSM group and the UC group, although this is not included as a specific aim.

We will consider interactions of treatment and the baseline value that would indicate the effect of treatment depends on status at baseline. We will also test for significant interactions of treatment with other variables (e.g., age, race, gender, and pain below the knee but not meeting criteria for sciatica) to determine if treatment differences are modified by these variables. To explore whether baseline characteristics predict which treatment performs better (Aim 3), we will examine our main outcome measures separately by subgroups using both tabular and graphical methods. We will begin with simple exploratory data analysis approaches, because we have no initial hypotheses about which characteristics will predict treatment success. Exploratory analysis will examine the univariate relationships between potential baseline predictor variables and outcomes of the treatments. We may also use more sophisticated statistical methods (e.g., latent class analysis) to identify individuals with different patterns of baseline characteristics that respond differently to the treatments.

We will also analyze secondary outcomes for Aims 1 and 2, including costs of back care, general health status (SF-36), depression, perceived stress, fear avoidance, disability days, and satisfaction with care. An analysis of costs may entail a transformation (e.g., log cost) but can be modeled using linear regression without a baseline value for costs since they will be unknown. We will adjust for age and other factors that may affect costs. We recognize that we will have low statistical power to detect even moderate cost differences among the groups. For binary outcomes (e.g., medication use) we will use logistic regression. Despite the multiplicity of analyses, we will focus our main analyses on treatment effects on each of the five outcome domains recommended for studies of back pain [8].

We are interested in the effect of individual massage therapists on the outcomes. Because each massage therapist will deliver both RM and FSM treatments, we can compare treatment effects within each massage therapist. While differences would have to be extremely large to detect a significant difference for a particular therapist, we may be able to determine whether there is significant variation across massage therapists that cannot be explained by random variation.

Finally, we will conduct exploratory analyses using the treatment log data to examine relationships among underlying conditions, treatments used and treatment outcomes. For the FSM treatment group, we will describe the frequency with which each specific technique was used and the relationship between the underlying condition and the technique(s) selected, using chi-square tests. We will then examine the relationship between the underlying condition and the likelihood of a good outcome and whether this relationship is affected by the specific treatment(s) employed. For these analyses we will use standard multivariate techniques (e.g., analysis of covariance, logistic regression, GEE). For the RM group, which follows a relatively fixed treatment protocol, we will only examine the relationship between the underlying condition and treatment outcomes.

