### Randomization to treatment groups

After administering the baseline questionnaire, the RS will use an ACCESS database to randomize one third of the participants to usual care and two-thirds to a massage intervention. The RS will ask the participants randomized to a massage treatment about their preference for geographic location of a therapist. The RS will then identify a therapist in the chosen location and enter that therapist's study identification code into the ACCESS database program that will use a pre-programmed computer-generated sequence of blocked random numbers for each therapist to assign the participant, with equal probability, to FSM or RM treatment. Thus, using this two-stage randomization procedure, roughly one-third of all participants will be randomized to each of the three arms. This will also ensure that each massage therapist sees approximately equal numbers of participants in each of the two massage groups. The one-third of participants randomized to the control group will be mailed checks for $50. The randomization database will be built to ensure that treatment allocation cannot be viewed prior to randomization and cannot be changed after randomization.

Participants randomized to the control group will be thanked for their willingness to participate, reminded of the importance of completing the follow-up interviews, and told they will be mailed checks for $50 in 4 to 6 weeks. Shortly after randomization to massage, the RS will call the massage therapist to provide the participant's contact information and to specify which type of massage the participant is to receive. The RS will also give the massage therapist a date by which the first appointment needs to be scheduled for that participant. Participants randomized to a massage treatment will be telephoned within 48 hours by the chosen massage therapist to set up the initial appointment. The massage therapist will call the research assistant to confirm that the first appointment has been made. The massage therapist will provide participants directions to the therapist's office. The massage therapist will schedule the nine subsequent visits with the participant.

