### Massage therapists

All massage treatments will be performed by licensed massage therapists who have at least 5 years experience, are comfortable strictly following both treatment protocols, and are trained and experienced in the techniques permitted in both the RM and FSM treatment protocols. Approximately 25 massage therapists in the Puget Sound region of western Washington will be recruited from within the network of alternative providers contracted to provide services to Group Health members. This will ensure that the therapists have already met minimum qualifications (e.g., massage training and licensure, malpractice insurance coverage, accessible and adequate treatment facilities). Participating massage therapists will need to agree to strictly adhere to the treatment protocols, be comfortable providing either massage treatment to any of the study participants, and to complete the training program for the study.

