### Statistical Issues

#### Sample size and the detectable difference

Because patient function (or dysfunction) is generally considered the more consequential of our two primary outcome measures, we want to ensure that our sample size estimates provide adequate power to detect a clinically significant difference of 2.0 points between groups on the Roland Disability scale [10]. To obtain outcomes data for 120 subjects per group, assuming a 10% loss to follow-up rate, we would need to randomize 133 participants. Our target sample size of 399 randomized individuals (133 per group) was computed using assumptions described below.

To protect against multiple comparisons, we will use Fisher's protected least significant difference approach which has been shown to have desirable properties when there are three groups [23]. This approach makes pair-wise comparisons between the three treatment groups only if the overall F-test is significant. The power of the overall analysis depends on how the means from the three treatment groups differ. We therefore assumed that the FSM group would be one Roland point superior to the RM group, which would, in turn, be one Roland point better than the UC group (giving a difference of 2 points between the FSM and UC groups).

Our estimates of the standard deviations of our primary outcome measures (adjusted for pre-randomization baseline values) derive from analyses of covariance of 8-week follow-up data from 92 study participants in our pilot study evaluating acupuncture for chronic low back pain: Roland SD = 4.65 and Bothersomeness SD = 2.71. Comparable standard deviation estimates at the end of the 10-week treatment period for 83 participants in our pilot study of CAM therapies for chronic low back pain, were 12%-15% lower. Thus, the standard deviation estimates we used for calculating statistical power in the proposed trial are probably conservative, likely underestimating actual power.

With 120 respondents per group (using two-sided significance level of 0.05) the omnibus F-test for the Roland scale will have 85% power for detecting a statistically significant difference among the three treatment means. If this omnibus test is statistically significant, as appears likely given our previous studies of FSM and those of others, we will address each Specific Aim of the study by comparing specified pairs of means, as discussed below. We will have 91% power to detect a pairwise difference of 2.0 Roland units.

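### The primary GEE leaves out the massage therapist, so if outcomes vary by therapist the massage-versus-usual-care standard errors are modestly too small

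*Protocol article*

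**What the plan says.** Under Statistical Analysis, the primary model is a linear mean model with baseline value, treatment, time and other covariates: "The models will be fitted using Generalized Estimating Equations (GEE) to take into account possible correlation within individuals over time". The abstract agrees. It names participant correlation and adjustment for baseline value, age and sex. The further covariates mentioned under Sample size and the detectable difference are baseline characteristics, and therapist is not one of them.

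On the design, the section Massage therapists states: "Approximately 25 massage therapists in the Puget Sound region of western Washington will be recruited". Under Randomization to treatment groups, participants first go to massage or usual care. Those sent to massage are then matched to a therapist by preferred location and allocated to FSM or RM from a "pre-programmed computer-generated sequence of blocked random numbers for each therapist". Usual care participants never acquire a therapist.

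Therapists return only late in Statistical Analysis: "We are interested in the effect of individual massage therapists on the outcomes". That paragraph plans to look at treatment effects within therapist and at variation between therapists. It does not link this to the tests of Aims 1 and 2.

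The power statements are "With 120 respondents per group (using two-sided significance level of 0.05) the omnibus F-test for the Roland scale will have 85% power" and "We will have 91% power to detect a pairwise difference of 2.0 Roland units", based on "Roland SD = 4.65 and Bothersomeness SD = 2.71". Neither contains a clustering term.

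**The concern.** Participants in the massage arms are nested in therapists, while RM and FSM are crossed with therapist. The primary model treats all participants as independent.

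Two participants treated by the same therapist may have correlated outcomes. A massage-arm mean then carries a therapist component that the usual care mean lacks. A sandwich estimator at participant level does not capture this, because it protects only against a wrong correlation among one person's repeated scores. The omnibus test that gates the pairwise tests uses the same variance.

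Some therapist variation is plausible. Therapists may tailor treatment, and most FSM techniques are left to their discretion. The primary aim, RM vs UC, would then be tested with a standard error that is too small. For Aim 2 (FSM vs RM), the analysis leaves out the factor within which the two arms were randomised.

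**Working it through.** **Inputs from the protocol article.** Analysed n = 120 per arm, two-sided alpha 0.05, Roland SD 4.65, pairwise difference 2.0 points, omnibus means spaced one point apart ("the FSM group would be one Roland point superior to the RM group", and RM one point better than UC), about 25 therapists.

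**Assumptions.** Therapist ICC (rho) from 0.01 to 0.10, which the documents do not give. Equal loads, so m = 120/25 = 4.8 analysed participants per therapist per arm.

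**The plan's own figures.** With independent participants the SE is 4.65 × sqrt(2/120) = 0.600. Pairwise power for 2.0 points is 91.5% (91.3% by noncentral t), against 91% stated. Omnibus power for means 0/1/2 is 85.3%, against 85% stated. Both reproduce.

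**Massage vs UC.** Only one arm is clustered, so

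SE = SD × sqrt[1/n + (1 + (m − 1)rho)/n],

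and the ratio to the planned SE is sqrt[(2 + 3.8 rho)/2]. Actual alpha is 2 × [1 − Phi(1.96/ratio)]. Power at the true SE is Phi(2/SE − 1.96).

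| rho | SE ratio | ungated alpha | power, 2.0 points |
|---|---|---|---|
| 0.01 | 1.009 | 0.052 | 91.0% |
| 0.02 | 1.019 | 0.054 | 90.5% |
| 0.05 | 1.046 | 0.061 | 88.9% |
| 0.10 | 1.091 | 0.072 | 86.3% |

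A simulation of a single time point (20,000 runs per ICC) gave alpha 0.056, 0.062 and 0.075 at rho 0.02, 0.05 and 0.10.

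**Uneven loads.** Participants choose the location, so equal loads are unlikely. With an assumed coefficient of variation of 0.6, the massage-arm design effect is 1 + [(1 + 0.36) × 4.8 − 1] × rho. This gives alpha of about 0.066 at rho 0.05 and 0.083 at 0.10.

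**The omnibus gate.** Pairwise tests follow only a significant overall test. In simulation with all three arms equal, the gated RM vs UC rejection rate is about 2.4%, 3.1% and 3.9% at rho 0, 0.05 and 0.10. If FSM works and RM does not, the gate nearly always opens and the rate is about 5.9% at rho 0.05 and 7.1% at 0.10.

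**FSM vs RM.** Let r be the correlation between a therapist's effects in the two arms. The variance is 2 × SD² × [(1 − rho) + m × rho × (1 − r)]/n. It equals the planned variance when m(1 − r) = 1, that is r = 1 − 1/4.8 = 0.79. For rho 0.01 to 0.10:

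| r | SE ratio | alpha |
|---|---|---|
| 1 | 0.995 to 0.949 | 0.049 to 0.039 |
| 0.5 | 1.007 to 1.068 | 0.052 to 0.066 |
| 0 | 1.019 to 1.175 | 0.054 to 0.095 |

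Simulation with r = 1 gave 0.044 and 0.039 at rho 0.05 and 0.10. At rho 0.02 it gave 0.052, so there the conservative effect was too small to see.

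**The case against.** The strongest reply is that the effect may be absent or small. The ICC is assumed. Therapists have at least five years' experience, common training, audits and booster training, and RM has bounded techniques and times, all of which should limit therapist variance. Therapists are chosen by location after the massage-or-usual-care allocation. Between-therapist differences that merely reflect where patients live would therefore not inflate the variance of RM vs UC, and only the therapist-induced part of the ICC counts. The gate also keeps the RM vs UC error below 5% when all arms are equal. All of this stands. It makes the point conditional and modest but does not remove it.

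On power, the protocol notes comparable pilot SDs 12% to 15% lower. With an SD 12% lower, power for 2 points is still about 95% at rho 0.05 and 93% at 0.10. That answers the power loss but not the type I error.

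It can also be said that the covariate vector is left open and that a fuller analysis plan may exist. This helps little. The article names the error structure, and therapist cannot simply be added as a covariate when a third of participants have none.

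A reader might infer that the standard errors are wrong in opposite directions, too small against usual care and too large for FSM vs RM. The documents do not support the second half. It needs a therapist's effects in the two arms to correlate above about 0.79, and the protocol itself allows for treatment effects that differ between therapists.

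**Conclusion.** The point holds in conditional form. As written, the primary model ignores a factor that the trial randomises by and that groups participants in two of three arms. The separate therapist analysis does not correct the tests of Aims 1 and 2.

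If the therapist-induced ICC is above zero, the planned standard errors for massage vs usual care are too small: by about 1% to 8% of the true value for an ICC of 0.01 to 0.10 with equal loads, and by more with uneven loads. The inflation of the RM vs UC error rate is realised mainly when FSM works and RM does not. For FSM vs RM the standard error is also misstated unless the two effects happen to offset, but its direction is open.

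The stated 85% and 91% are correct for independent participants. This should be changed before unblinded data are seen, but it does not threaten the trial.

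**What to change.** State that one primary three-arm model, used for both the omnibus test and the pairwise comparisons, accounts for therapist. Two forms would do:

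- a partially nested mixed model with a therapist random effect in the massage arms only and a therapist-by-treatment variance term, keeping the within-participant correlation over time;
- GEE with sandwich errors, with therapist as the cluster for massage participants and each usual care participant as a cluster of one, and a small-sample correction for about 25 clusters.

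The therapist-by-treatment term should not be left to exploratory work. A shared therapist effect alone would shrink the FSM vs RM standard error on the strength of the very assumption that is in doubt. Using a single model also keeps the omnibus gate coherent. Show power over a range of ICCs, including uneven loads.

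No new data are needed, since the therapist code is entered at randomisation. The price is a somewhat more complex model and a slightly larger massage-vs-usual-care standard error, about 5% at an ICC of 0.05. With about five participants per therapist per arm, the therapist-by-treatment variance will be estimated imprecisely. Naming the model in advance avoids a later choice between analyses that could give different p-values for the primary aim.

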## Methods and Design

### Overview

We will recruit health plan patients who have sought medical care for chronic low back pain. Eligible participants will be randomized equally to one of three groups (Figure 1): Relaxation Massage (RM), Focused Structural Massage (FSM) or continued usual care (UC). Participants in the two massage arms will receive 10 treatments over a 10-week period. The massage treatments will be provided by licensed massage therapists with experience in both RM and FSM and who will receive special training in implementation of the treatment protocols. To minimize disappointment (and possibly losses to follow-up), participants assigned to UC will receive $50. All participants will retain access to the health care services to which they are entitled by their insurance coverage.

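### The missing-data correction depends on finding differential dropout, a check that would often miss moderate imbalance at the planned 10% loss

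*Protocol article*

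**What the plan says.** The Statistical Analysis section describes a regression of follow-up scores on baseline value, treatment, time and other covariates. It is fitted by GEE to every interview a participant completes, and no weighting is mentioned. The section then adds a preliminary step: "it is important to first assess whether there is differential dropout by either assigned treatment or symptom or function level". The consequence is conditional: "If differential dropout occurs, we will use the method of Little to rectify possible biases that could occur". No test, significance level or threshold is attached to that decision. No correction or sensitivity analysis is described for the case where the look is negative.

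Three other places bear on the point. The sample size section assumes 10% loss. The section on primary measures makes week 10, the first follow-up, the primary endpoint. The Overview shows that unequal loss was considered possible: "To minimize disappointment (and possibly losses to follow-up), participants assigned to UC will receive $50".

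**The concern.** The choice between an uncorrected and a corrected analysis is left to what the dropout data happen to show. With few dropouts, a negative result says little about whether dropout is harmless, yet under this plan it ends the matter. The wording also describes looking by arm or by level. It does not describe asking whether the relation between level and dropout differs between arms. If the worse-off left usual care and the recovered left massage at similar rates, both looks could be reassuring while the contrast between arms is biased.

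At stake are the comparisons with usual care. The primary aim, RM v UC, was planned around a 1-point Roland difference, so a bias of a few tenths of a point matters there more than it does against the 2-point FSM v UC difference.

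**Working it through.** **The plan's own figures.** The inputs come from the sample size section: "using two-sided significance level of 0.05", "Roland SD = 4.65 and Bothersomeness SD = 2.71", and equally spaced means "giving a difference of 2 points between the FSM and UC groups".

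- Randomized per arm: 120 / 0.90 = 133.3 (stated 133).
- Omnibus test: noncentrality = n Σ(μᵢ − μ̄)² / σ² = 120 × 2 / 4.65² = 11.1. Power is 85.3%, against "the omnibus F-test for the Roland scale will have 85% power".
- Pairwise: 2.0 / (4.65 × √(2/120)) = 2.0 / 0.600 = 3.33. Power is 91.5%, against "We will have 91% power to detect a pairwise difference of 2.0 Roland units".

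These reproduce. Expected losses are 0.10 × 399 ≈ 40 (about 13 per arm), leaving 359 completers.

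**Power of a check by arm.** The article gives no figure, so a 0.05-level chi-square test on 2 df is assumed. Noncentrality = 133 Σ(pᵢ − p̄)² / [p̄(1 − p̄)] with p̄ = 0.10. For 7/10/13% this is 133 × 0.0018 / 0.09 = 2.66.

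| Dropout by arm | Noncentrality | Power |
|---|---|---|
| 8/10/12% | 1.18 | 15% |
| 7/10/13% | 2.66 | 29% |
| 6/10/14% | 4.73 | 48% |
| 5/10/15% | 7.39 | 68% |
| 3/10/17% | 14.5 | 94% |
| 5/5/20% | 22.2 | 99% |

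**Power of a check by level.** Comparing 40 dropouts with 359 completers, the standard error of a standardized difference is √(1/40 + 1/359) = 0.167. Power is 22% at a difference of 0.2, 44% at 0.3, 67% at 0.4 and 85% at 0.5.

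**Both checks together.** This was simulated with 133 per arm and 500 runs per case. Assumptions that are not in the article: baseline SD 5, slope 0.5 on baseline, residual correlation over time 0.6, and a dropout log-odds ratio of 0.4 or 0.8 per SD.

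- *Opposite directions, 10% loss in every arm.* Either check is positive in 10-13% of runs. Two independent 0.05-level tests of nothing would give 1 − 0.95² = 9.8%. When the score driving dropout is observed, an arm-by-level interaction test flags 92% of runs at a log-odds ratio of 0.8 and 35% at 0.4. When the driver is the unseen 10-week score and only baseline can be tested, it flags 33% at 0.8.
- *Dropout related to the unseen 10-week score, 13/10/7% (UC/RM/FSM), log-odds ratio 0.8.* The arm check is positive in 31% of runs, the baseline-level check in 53%, and either one in 65%.
- *Strong dependence on an observed level, same in all arms (0.8 per SD).* The level check is positive in about 99% of runs.

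**Bias of the default analysis.** These are large-sample simulations on the same assumptions, with true differences of −1 (RM v UC) and −2 (FSM v UC) and Monte Carlo error about 0.02. The week 52 rows use an independence working correlation, which is a further assumption.

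| Dropout mechanism | RM v UC | FSM v UC |
|---|---|---|
| Week 10: baseline only, same or differing by arm | about 0 | about 0 |
| Week 10: unseen score, 13/10/7% | 0.08 | 0.20 |
| Week 10: unseen score, opposite directions, equal rates | 0.17-0.33 | 0.33-0.60 |
| Week 52: observed 10-week score, 13/10/7% | 0.04 | 0.13 |
| Week 52: observed 10-week score, opposite directions, equal rates | 0.11-0.20 | 0.20-0.39 |

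In these cases the bias makes massage look less effective than it is; the reverse pattern would flatter it. When dropout depends on the score equally in all arms at equal rates, the contrasts are close to unbiased. Week 26 was not simulated, but the week 52 mechanism applies to it too.

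A hand check of the size at week 10: if UC loses 6 percentage points more than FSM, and leavers are 4 to 5 points worse than stayers on the unseen score (assumed), the contrast shifts by 0.06 × 4 = 0.24 to 0.06 × 5 = 0.30.

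**The case against.** The article anticipates dropout, names a correction, and is a condensed account whose analysis plan is not shown. The definition of the check may well be given there, and its absence is not the complaint. The complaint is the stated rule itself, under which correction follows only a positive finding.

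Several stronger readings are tempting, and the article does not support them.

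- *That the default GEE is valid only if data are missing completely at random.* The model conditions on treatment and baseline value, and the sample size section plans to add age, gender and predictive baseline covariates. Dropout that depends only on modelled variables does not bias a correctly specified mean model, and the simulation found about zero bias there.
- *That the correction would be skipped about two times in three.* That counts only the look by arm. In the 13/10/7% case tied to the unseen score, either look is positive in 65% of runs. The 0.05 level is also an assumption, and large imbalance would be found.
- *That the plan expects losses from disappointment in usual care.* The Overview says only possibly, and offers a payment to prevent it. Participants must also be willing to complete all three follow-ups, and withdrawals are to be recorded by reason.
- *That a missing-at-random method would cure the primary endpoint.* Week 10 is the first follow-up, so baseline is the only earlier measurement of the outcome. Bias there comes mainly from the unseen score, and such a method removes it only so far as observed data predict that score.

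These points narrow the concern. They do not justify doing nothing after a negative look, because no check on observed data can rule out dropout tied to unseen scores.

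**Conclusion.** The point holds in a limited form. The article makes the missing-data correction depend on a look that, at about 40 losses, would often miss moderate imbalance, and that would mostly miss opposite-direction dropout if arm and level are examined separately. The analysis left standing can then be biased: at weeks 26 and 52 if dropout depends on earlier follow-up scores, and at week 10 if it relates to the unseen score.

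The plausible size at week 10 is about 0.1 to 0.6 Roland points across the two contrasts with usual care, and 0.08 to 0.33 for RM v UC. That is modest against the 2-point target but not negligible against the 1-point RM v UC difference. The power figures rest on an assumed 0.05 test and chosen dropout rates. The bias figures rest on the simulation assumptions listed above. The reference cited for the correction was not available, and nothing here relies on its content. This is a worthwhile, inexpensive improvement; it does not show that the trial's result would be wrong.

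**What to change.** Make the handling of missing data unconditional.

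1. Pre-specify one primary analysis that is valid under missing at random, uses all completed interviews and is applied whatever the dropout pattern. Examples are a likelihood-based repeated-measures model, or GEE with multiple imputation or inverse-probability weighting. Keep the 10-week contrast as primary.
2. Always report a sensitivity analysis that allows data to be missing not at random, with assumptions that may differ by arm. This matters most at week 10, where step 1 alone does not remove the bias.
3. Keep the comparison of dropout by arm and by level as description only, with no bearing on which estimator is reported.

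The first step addresses weeks 26 and 52, and the second shows how far the week 10 result depends on unseen scores. The cost is a change of wording and modest programming, with no new data. The drawback is reliance on a covariance, imputation or weighting model, which should be fixed in advance.
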